Abdominal obesity has been suggested to be associated with overstimulation of the hypothalamic-pituitary-adrenal (HPA) axis [23,24] due to chronic stress [25], altering diurnal cortisol secretion. Abnormal regulation of the HPA axis and perceived stress-dependent cortisol levels are strongly related to perturbations of the endocrine axis as well as abdominal obesity with metabolic abnormalities [26].

A complex set of interrelationships occur between lifestyle, anthropometric, psychological and physical activity variables [27]. Of particular interest is the apparent relationship between physical and mental health [28,29]. Depressed people generally have lower physical activity levels than people without depression [30,31]. Lower physical activity levels also exacerbate depression resulting in a negative feedback cycle [32]. Conversely, increasing physical activity has the dual benefit of increasing physical fitness and alleviating depression and anxiety [29]. Even without the physical health benefits, increasing physical activity may block negative thoughts, distract people from worries, increase social contact and change the brain chemistry to improve mood [33]. Farming people are seldom thought of as being physically inactive, however the very nature of farming is seasonal, increasingly mechanised, with longer periods of being sedentary and greater reliance on vehicles. Further, opportunities for leisure time activity are reduced since many local sporting clubs have amalgamated or ceased to exist and access to a gymnasium or personal trainers is likely to be difficult due to distance and financial constraints.

The aim of this paper is to describe the pilot testing of the Farming Fit study which will examine the effect of physical activity on psychological health, obesity, impaired glucose tolerance, hypertension and dyslipidaemia in farm men and women.

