## Methods/Design

### Intervention community

Inclusion - Farm men and women participating in SFF programs will be recruited. Participants will be recruited from rural Victoria, have been farming for more than 5 years, be aged between 18 and 75 years, speak English and live 10 kilometres or more from a regional centre with a population greater than 10, 000. All study participants will be either overweight or obese as determined by body mass index (BMI) ≥ 25 kg/m^2^.

Exclusion - Participants will be excluded from the study if they have a chronic terminal illness or are pregnant or lactating mothers. People with very high levels of psychological distress will be referred for mental health assessment by a health professional (DASS 21 Score depression > 28 or anxiety > 20 or stress > 37) [33]. Subjects unable to participate in physical activity will not be eligible to participate.

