### Sample size

To evaluate the intervention, sample size was determined at the power of 80% (β = 0.2) with α set at 0.05 for an effect size of a standard deviation change of fasting serum cortisol and/or a 0.5 standard deviation reduction of body weight by the end of the intervention. This required the sample size to be a minimum of 64 participants across the control and intervention groups [37]. By considering the probable retention rate (≥95%) for a 6-month intervention the target recruitment number was fixed at a minimum of 35 participants in both the control and intervention groups, requiring recruitment of a total of 70 farming participants meeting the above criteria.

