#### Cortisol measurements

The cortisol response is consistently enhanced under chronic stress conditions and studies have demonstrated that the free cortisol response can serve as a useful index of hypothalamo-pituitary-adrenal axis (HPA) activity [26]. The secretion of cortisol, which is a marker of HPA axis activity, follows a diurnal pattern with peak levels following awakening and declining levels thereafter [44]. In this study, fasting blood cortisol will be measured in addition to salivary cortisol. Assessment of cortisol in saliva is a widely accepted and frequently employed method and is considered a valid and reliable reflection of the respective unbound hormone in blood [45]. Due to several advantages over blood cortisol analyses (e.g. stress-free sampling, less intrusive, lower costs), salivary cortisol assessment is the preferred method in basic research and clinical environments. Salivary cortisol is now an accepted, convenient method that is used to provide an indication of the variation of cortisol secretion throughout the day [45]. Salivary cortisol correlates with serum/plasma cortisol concentrations [45] and is stable at room temperature for up to 7-days [46]. Pregnancy, physical and emotional stress, strenuous activity, infection, injury and illness can increase cortisol levels. A number of drugs can also increase levels, particularly oral contraceptives (birth control pills), hydrocortisone (the synthetic form of cortisol), prednisolone and spironolactone. Therefore, the medication history of study participants will also be collected during the study.

Three groups of saliva samples will be collected using the Salivette sampling device (Sarstedt, Rommelsdorf, Germany) at baseline, three months and six months. Participants will be requested to abstain from smoking, ingesting caffeine, alcohol, food and all fluids, and strenuous physical activity for 1 h before each saliva collection. A saliva sample will be collected at approximately 09:00 hour, 12:00 hour, 16:00 hour and 20:00 hour. All saliva samples will be stored at room temperature and then spun at 3,000 × *g *for 5 min within 5 days of collection. Spun samples will be stored at -80°C until saliva cortisol levels are assayed by Radioimmunology assay (Orion Spectra Cortisol^®^).

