#### Data entry, handling and statistical analysis

Data will be tabulated and analysed using PASW^® ^statistics 18 software. Variables will be reported as means with 95% confidence intervals. Repeated measures ANOVA, paired sample t-tests, multiple linear regression, and binary logistic regression will be used to test for intervention effects after adjusting for relevant co-variables (e.g. sex, age) and baseline scores. Since physical activity scores are likely to reflect a non-normal distribution, comparisons between the sexes at baseline and over time will be performed using the Kruskal-Wallis test. Linear regression analysis will be used to assess the association between body fat percentage, body mass index and cortisol levels. Correlation coefficients between body composition, physical activity, and metabolic variables will be calculated using Pearson's and Spearman's correlation as appropriate. P values will be considered statistically significant at P < 0.05.

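### The correlations among body composition, activity and metabolic variables, and the adiposity-cortisol regression, are stated without the sex and age adjustment that the plan gives to its intervention tests (minor)

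*Protocol article*

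**What the plan says.** All the relevant analysis text is in the protocol article, under the heading *Data entry, handling and statistical analysis*.

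- **Intervention tests.** Repeated measures ANOVA, paired t-tests, multiple linear regression and logistic regression "will be used to test for intervention effects after adjusting for relevant co-variables (e.g. sex, age) and baseline scores".
- **Activity scores.** Because these are expected to be non-normal, "comparisons between the sexes at baseline and over time will be performed using the Kruskal-Wallis test".
- **Adiposity and cortisol.** "Linear regression analysis will be used to assess the association between body fat percentage, body mass index and cortisol levels". No covariate is named.
- **Correlations.** "Correlation coefficients between body composition, physical activity, and metabolic variables will be calculated using Pearson's and Spearman's correlation as appropriate". No partial or sex-specific version is named.
- **Threshold.** The paragraph closes with a 0.05 significance level and exempts none of these analyses.

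Under *Intervention community*, the sample includes both sexes: "Farm men and women participating in SFF programs will be recruited". Age and gender are collected (section *Psychosocial assessment*).

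**The concern.** The Background gives the reason for looking at these associations, and it is physiological: "perceived stress-dependent cortisol levels are strongly related to perturbations of the endocrine axis as well as abdominal obesity with metabolic abnormalities". A question of that kind is about people of the same sex who differ in adiposity. A coefficient computed over men and women together does not isolate it. Part of the coefficient is the within-sex association, and part reflects any difference between the average man and the average woman on the two variables.

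The plan itself treats sex as a relevant covariate for the intervention tests and expects to compare activity between the sexes, and activity is one of the correlated variables. Followed as written, the correlations carry no sex adjustment. A significant pooled result could then be reported as support for the adiposity-cortisol or adiposity-metabolic link when it comes partly or wholly from the sex mix. A real link could also be weakened or missed.

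**Working it through.** The plan gives no figure of its own for these analyses, so there is nothing to reproduce. The check is how far a pooled coefficient can move from the within-sex one.

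**Inputs from the article.** Total recruitment is 70 and alpha is 0.05 (section *Sample size*); the significance threshold is P < 0.05 (statistical analysis section).

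**Assumptions, because the article gives no value.** Tests are two-sided; all 70 participants contribute one observation; half are women (p = 0.5); SDs within each sex are equal to 1; the sex gaps dx and dy are in within-sex SDs.

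**Formula.** With within-sex correlation ρ,

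pooled r = (ρ + p(1−p)·dx·dy) / √[(1 + p(1−p)·dx²)(1 + p(1−p)·dy²)]

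With p = 0.5, p(1−p) = 0.25.

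**A. No link in either sex (ρ = 0).** For example, gaps of 2.0 and 0.5 give 0.25 × 2.0 × 0.5 = 0.25 in the numerator and √(2 × 1.0625) = 1.458 in the denominator, so pooled r = 0.17. Rejection rates below come from simulating the pooled Pearson test and the sex-adjusted test.

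| Gaps (dx / dy) | Pooled r | Pooled test significant | With sex term |
|---|---|---|---|
| 2.0 / 0 | 0.00 | 5% | 5% |
| 2.0 / 0.3 | 0.10 | 13% | 5% |
| 1.0 / 0.5 | 0.11 | 15% | 5% |
| 1.5 / 0.5 | 0.15 | 23% | 5% |
| 2.0 / 0.5 | 0.17 | 30% | 5% |
| 1.5 / 0.8 | 0.22 | 48% | 5% |
| 2.0 / 0.8 | 0.26 | 62% | 5% |

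A false link needs a sex gap in both variables; a gap in one alone leaves the level at 5%. An uneven sex split reduces the distortion but does not remove it: with 30% women, gaps of 2.0/0.5 give 24% and 1.5/0.8 give 38%.

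**B. A real link in both sexes (ρ = 0.35), with only body fat differing by sex (dy = 0).**

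- Gap 1.5: pooled r = 0.35 / √(1 + 0.25 × 2.25) = 0.35 / 1.25 = 0.28; power about 67%.
- Gap 2.0: pooled r = 0.35 / √2 = 0.25; power about 55%.
- With a sex term, power is about 85% in both cases.

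**C. The same real link, with the cortisol gap running the opposite way to the body-fat gap of 2.0.**

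- Cortisol gap 0.3: pooled r = (0.35 − 0.15) / 1.430 = 0.14; power about 20%.
- Cortisol gap 0.5: pooled r = (0.35 − 0.25) / 1.458 = 0.07; power about 6%.
- With a sex term, power is again about 85%.

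**The case against.** The strongest reply is that this reads silence as a statement. The regression sentence lists no covariates, but it does not say that the model is unadjusted. The article is condensed, and a full protocol or analysis plan may name the covariates of secondary models. For the regression this largely stands: the absence of a sex term is inferred from the contrast with the intervention sentence in the same paragraph. It stands less well for the correlations. Pearson's and Spearman's coefficients are bivariate, so the method named carries no adjustment unless a partial or sex-specific version is specified.

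The second reply is that the sex gaps have no basis in the document. That also stands as to size. The article gives no sex-specific values for body fat, cortisol or lipids. Oral contraceptives are named under *Cortisol measurements* as raising cortisol, but alongside other drugs, and the stated response is to record medication history; this shows a possible sex-linked influence and gives no gap. Pregnancy, also named there, lends no support, because pregnant women are excluded. Planning a sex comparison of activity does not assert a difference.

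Third, these analyses are ancillary. The stated aim is the effect of physical activity, and those tests are adjusted. This stands and limits the severity.

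A reader might go further and infer that the pooled analyses merely test whether the sexes differ on both variables. That is not supported: the pooled coefficient contains both within-sex and between-sex association, and it is a pure sex contrast only when the within-sex association is zero.

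**Conclusion.** The point holds as a minor one. It is firm for the correlations, where the stated method is unadjusted, and weaker for the regression, where no covariate is named.

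Under the assumptions listed, a pooled test can have a false-positive rate of about 15% to 62% when the gaps are 1.0-2.0 SD in one variable and 0.5-0.8 SD in the other. The rate is about 13% at 2.0/0.3 SD and 5% when only one variable differs by sex. A body-fat gap of 1.5-2.0 SD alone cuts power for a within-sex correlation of 0.35 from about 85% to 55-67%. If neither variable differs by sex, nothing is lost by pooling.

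A reader might infer that the trial's main result is at risk. It is not: the intervention comparison has its own stated adjustment, and neither it nor the sample size depends on these analyses.

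**What to change.** In the statistical analysis section, extend the adjustment already stated for intervention effects to the association analyses:

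- Replace the simple correlations with partial correlations (Pearson or rank) adjusted for sex and age, or report them by sex.
- Include sex and age as covariates in the adiposity-cortisol regression.
- Add scatterplots marked by sex as a check.

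The partial version is preferable for testing. With 35 per sex, a single-sex test of r = 0.35 has power of only about 54%: artanh(0.35) = 0.365, times √32 = 2.07, and Φ(2.07 − 1.96) = 0.54. Sex-specific coefficients are still useful as description.

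The cost is one or two sentences of text and about two degrees of freedom (68 to 66 for a correlation on 70 participants). Sex and age are already collected, and the planned sample size does not change.

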### Consent and ethics

All adults participating in the study will be provided with a plain language statement and will provide informed written consent. Ethics approval has been granted for the project by Deakin University Human Research Ethics Committee (2009/215) and the South West Multidisciplinary Ethics Committee (HREC 2009/215 dated 03/02/2010). All researchers involved in data collection have had a Victorian Police check undertaken.

## Discussion

Rural populations face poor outcomes in mental health and associated co-morbidities of obesity, diabetes and cardiovascular disease [6-10]. Farming populations are a subset of this group that face additional challenges due to the tyranny of distance, access to health services, stigma associated with mental health issues and the distance-decay effect[6,12,13]. They currently have a high mental health burden and higher rates of obesity and associated health consequences[20]. This study aims to determine the effect of physical activity with coaching on psychological health and biochemical levels of serum cholesterol, triglycerides, LDL, HDL, fasting blood glucose and cortisol in a population of overweight and obese farm men and women. The outcome results of this study will be used in further research and service delivery programs for farming communities.

## List of abbreviations

**SFF**: Sustainable Farm Families™; **K-10**: Kessler 10; **HPA**: Hypothalamus Pituitary Adrenal; **LDL**: Low Density Lipoproteins; **HDL**: High Density Lipoproteins; **DASS-21**: Depression, Anxiety, Stress Score-21; **WC**: waist circumference; **BMI**: Body Mass Index.
